**Figure 1 figure1:**
[figure not shown]
Study design.

### Analytic Strategy

Effects of time and group (main outcomes: subjective and objective measures of PA) will be examined in multivariate analyses. In addition, covariates, such as gender, age, and preferences regarding intervention material, and individual contextual factors (eg, living or social environment) will be taken into account. Furthermore, we will analyze how the intervention enables study participants to change their behavior by running mediation analyses. The estimated target sample size of 390 participants for this study is based on the results of 2 recently published studies on PA in adults [27,28] that reported a mean 111 weekly minutes (SD 116.8 weekly minutes) of MVPA and an intervention effect of an increase in MVPA of 77 minutes per week. However, in a conservative (or realistic) approach, we assumed that the mean increase in MVPA in our study will reach only 40 minutes/week. To detect such a difference between the intervention and control groups with a power of 80% at an alpha of .05 (two-sided), a net sample size of 150 subjects for each group is required. Assuming a loss to follow-up from T0 to T1 of 20-25% (ie, ca. 23%), it is necessary to initially recruit 390 study participants (ie, 195 per group at baseline). Assuming another 20% loss to follow-up from T1 to T2, we expect that approximately 240 individuals at T2 will self-select to one of the 4 groups: IT-IT, print-print, IT-print, or print-IT. Should participants self-select equally into each group (n=60), we will still be able to detect the mean difference of 77 minutes/week [28] between each group, by means of an appropriate post hoc test that is adjusted for multiple comparisons.

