**Methods:**

Our target sample size was 390 initially inactive community-dwelling older adults aged ≥60 years at baseline (3-month follow-up [T1]: expected n=300; 9-month follow-up [T2]: expected n=240) who were randomized to one of two interventions for self-monitoring PA: IT-based (50%) or print-based (50%) intervention. In addition, 30% of the IT-based intervention group received a PA tracker. At T1, participants in both groups could choose whether they prefered to keep their assigned intervention or cross over to the other group for the following 6 months (T2). Participants’ intervention preferences at baseline were collected retrospectively to run a post hoc matched-mismatched analysis. During the initial 3-month intervention period, both intervention groups were offered weekly group sessions that were continued monthly between T1 and T2. A self-administered questionnaire and 3D accelerometers were employed to assess changes in PA between baseline, T1, and T2. Adherence to PA recommendations, attendance at group sessions, and acceptance of the interventions were also tracked.

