### Study Aims

Hence, based on previous findings of the literature and knowledge gained during the preceding trial, this study aimed to adapt and simplify the IT-based intervention of the first funding phase further to improve usability and develop a simple print-based intervention that initially inactive participants with little affinity to technology find easy to interact with; investigate the implementation, feasibility, and use of 2 interventions (IT-based vs print-based) as well as changes in PA among older adults (aged ≥60 years) in a randomized trial with a crossover design over the course of 9 months; examine the role of personal preferences for different delivery modes with regard to intervention effectiveness; and explore associations between changes in PA and possible changes in physical fitness and cognitive capacity in a pooled sample of participants from both phases of funding.

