### Study Design

After determination of eligibility, study participants were randomized to either an IT-based intervention or a print-based intervention (see Figure 1). In the first group, 30% were randomly selected to receive a PA tracker in addition to access to the website. Weekly time slots were randomly assigned to both intervention groups. Then, we had participants choose appointments according to their personal time constraints without knowing which intervention group they were assigned to. All intervention groups were offered weekly group sessions, and participants were encouraged to attend each of them. Two weeks before the intervention started, participants in all groups attended an introductory event where they were informed about the study background and procedures. On this day, data collection also started, and participants received the activity tracker and questionnaires for the first time (T0). They were also briefed about their randomization to one of the intervention groups and the existence of the other groups. Therefore, they were not blinded. Participants were given the choice to remain in their intervention group or to cross over to the other group after 3 months (and a 10-week intervention period). With that, a crossover design with the following possible combinations was generated: IT-IT, print-print (matched), or IT-print and print-IT. Preferences regarding the intervention material assessed retrospectively at the 9-month follow-up will be taken into account when analyzing intervention effects later in the study. Research staff members conducting the study were not blinded, and the statistician will not be blinded when analyzing the data.

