**Use of, acceptance of, and satisfaction with interventions**			
	Use and acceptance of various components of the interventions (website and printed material), attendance of the offered group sessions, and overall satisfaction with the interventions	Self-generated items	T1, T2
	Preference regarding intervention material at baseline (retrospective)	Self-generated item	T2
	Reasons for crossing over or not crossing over after 3 months	Self-generated items	T2

^a^Baseline.

^b^3-month follow-up.

^c^9-month follow-up.

^d^HAPA: Health Action Process Approach.

^e^PSDQ: Physical Self-Description Questionnaire.

^f^WHOQOL-BREF: World Health Organization Quality of Life-BREF.

^g^SF-36: Short Form 36.

^h^EQ-5D-3L: 3-level version of the EQ-5D.

^i^EFST: Elderly Fall Screening Test.

^j^GFFM: Geriatric Fear of Falling Measurement.

^k^FFQ: Food Frequency Questionnaire.

^l^AUDIT-C: Alcohol Use Disorders Identification Test Short Version.

^m^CES-D: Centers for Epidemiologic Studies Depression Scale.

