Last, complementing existing health and preventive care with eHealth intervention approaches, such as mobile apps for PA promotion, is in line with the current eHealth initiative of the Federal Ministry of Health [71]. The project is embedded in multidisciplinary research aimed at better understanding how changes in individual behavior and the environment and technology can help promote healthy aging. Our findings will inform the future development of complex interventions combining both local and regional policy changes aimed at promoting environmental changes and technology-based interventions targeting individual behavior change. Our experiences regarding this population’s data protection concerns will be communicated to policy makers currently involved in the eHealth initiative and will support the identification of suitable approaches to deal with these concerns.

Despite the advantages of the study design and objective PA measurement, several limitations can be identified. First, this study design does not include a control group, which might limit the interpretations that can be drawn from the potentially positive intervention effects. Second, the target population consists of inactive older adults, which are difficult to recruit. Third, the retrospective assessment of the preference for a certain intervention delivery mode, which could result in recall bias. However, we chose to retrospectively assess preferences because we anticipated disappointment (and possibly dropouts) if a person was not randomized to their preferred intervention group at baseline.

To conclude, this study will provide insights into the acceptance and effectiveness of an IT-based vs a print-based intervention for the promotion of PA in initially inactive individuals aged ≥60 years. In addition to answering the main research questions, we expect to obtain a better understanding of the interactions between numerous contextual factors and PA in this population. Results from this study will inform the work of various stakeholder groups actively involved in PA promotion at the population level and in different contexts and will support the shaping of new policies regulating the future design and implementation of preventive eHealth interventions for active aging.

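### Intervention preference, recalled only at month 9, is listed as a covariate for the randomised comparison and cannot carry the preference aim as planned

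*Protocol article*

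**What the plan says.** The Analytic Strategy section describes the main analysis as follows: "Effects of time and group (main outcomes: subjective and objective measures of PA) will be examined in multivariate analyses". It then adds that "covariates, such as gender, age, and preferences regarding intervention material, and individual contextual factors (eg, living or social environment) will be taken into account". Preference thus stands in the same list as gender and age.

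Study Design fixes when it is measured and how it will be used: "Preferences regarding the intervention material assessed retrospectively at the 9-month follow-up will be taken into account when analyzing intervention effects later in the study". Table 1 lists the item with T2 as its only time of assessment. Study Design also says that participants were told their allocation, and that the other groups existed, at the introductory event where baseline data collection began, so they were not blinded. The stay-or-switch choice came at 3 months.

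One of the Study Aims is to "examine the role of personal preferences for different delivery modes with regard to intervention effectiveness". The Abstract names the tool: "Participants’ intervention preferences at baseline were collected retrospectively to run a post hoc matched-mismatched analysis". The Discussion lists as a limitation "the retrospective assessment of the preference for a certain intervention delivery mode, which could result in recall bias", and explains that preference was not asked at baseline because disappointment and dropout were feared.

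**The concern.** Gender and age cannot be altered by the assigned intervention. A preference recalled after about nine months can be. Someone who did well with the assigned material may remember having wanted it, and someone who struggled may remember the opposite. Although labelled a baseline preference, it is a post-randomisation measurement that may depend on arm and outcome.

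Two consequences follow.

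- **The randomised comparison.** The variable does not exist for anyone lost before T2. A T1 model that needs it may lose participants who have T1 outcomes. The loss may not be random: the Introduction suggests that preference may have influenced dropout in earlier tracker trials, and the Methods account of the preceding study suggests that some participants were allocated to something too difficult for them.
- **The preference aim.** Participants are classed as matched or mismatched by comparing recalled preference with allocation. If recall drifts towards what worked, the matched group is enriched with people who did well, and a match effect appears where none exists.

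The Discussion's remark on recall bias mentions neither dependence on arm and outcome nor absence of the variable for those lost before T2.

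**Working it through.** **Inputs from the protocol (Abstract and Analytic Strategy).** 390 at baseline, 300 expected at T1, 240 at T2; 1:1 allocation; SD 116.8 min/week; difference 40 min/week; two-sided alpha .05; power 80%; 150 per group net.

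**1. The plan's own figures.** The attrition chain reproduces: 150/0.77 = 194.8, so 195 per group and 390 in total; 300 × 0.80 = 240. A two-sample t test with these inputs needs 135 per group for 80% power, so the stated 150 is conservative and gives 84.0%. That gap does not bear on this point.

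**2. Availability of the covariate.** 240/390 = 61.5%, so 150 of 390 (38.5%) have no recalled preference. Of the 300 with T1 data, 300 − 240 = 60 (20%) have none.

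**3. Power at T1 if the model uses complete cases (assumed).** The standard error is SD × √(2/n).

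| n per arm | Standard error (min/week) | 40/SE | Power (t test) |
|---|---|---|---|
| 150 | 116.8 × √(2/150) = 13.5 | 2.97 | 84.0% |
| 120 | 116.8 × √(2/120) = 15.1 | 2.65 | 75.2% |

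By the normal approximation, the difference detectable with 80% power rises from 37.8 to 42.2 min/week, past the planning value of 40.

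**4. Does the covariate bias the arm contrast?** Null simulation with 240 participants (120 per arm) and no true arm or match effect. Outcome y is standard normal, in units of 116.8 min/week, and arm is coded ±1. Latent preference = N(0,1) + k·y·arm + 0.5 × logistic noise; recalled preference is its sign. In the regression of y on arm plus recalled preference, the arm effect stays within 1 min/week of zero and rejection is about 5% to 6%. In a separate simulation where recall shifts in the IT arm only (log-odds shifts of 0.5 to 1.0), the adjusted arm effect moves by about −1 to −3 min/week.

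**5. Matched minus mismatched, same null simulation.** The shift k is assumed; nothing in the protocol fixes it, so a range is shown.

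| k (latent SD per SD of change) | Spurious difference (min/week) | False positives |
|---|---|---|
| 0.05 | about 7 | 7% |
| 0.1 | about 14 | 16% |
| 0.2 | about 27 to 28 | 44% to 47% |
| 0.3 | about 41 to 42 | 77% to 79% |
| 0.5 | about 66 | over 99% |

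Where a range is given within a row, it is Monte Carlo variation between runs.

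**The case against.** Several points on the other side have force.

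- **No preference interaction is placed in the main analysis.** A reader might infer that preference is an effect modifier in the randomised comparison. The Analytic Strategy names it only as a covariate, and the Abstract calls the matched-mismatched analysis post hoc. This stands.
- **No complete-case rule is stated.** A reader might infer that everyone lost before T2 will be dropped. The article gives no missing-data method, and a full analysis plan may. Imputation, or a T1 model without preference, would keep the 300. This stands, so the power loss is conditional. Imputed preference would still be learned only from people who stayed to T2.
- **The arm contrast is not shown to be biased by the adjustment.** With recall shifted equally in both arms, the covariate-adjusted effect is essentially unchanged, and even a one-arm shift moves it little. Bias from selective dropout is possible but has not been quantified.
- **The simulated size depends on an assumed input.** Any single figure, such as 41 min/week, is one point in a wide range and concerns only the matched-mismatched contrast.
- **Recall bias is disclosed and the design choice explained.** This stands in part. A general disclosure does not justify entering the variable in the model for the main outcomes, and the two specific consequences are not mentioned.

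**Conclusion.** The concern holds in limited form. Listing a T2-recalled preference beside age and gender as a covariate for the main outcomes is a stated analytic choice, and a poor one.

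For the randomised comparison, the likely harm is loss of participants and power: from 84% to 75% at T1, below the planned 80%, if complete cases are used. Retention may also be related to mismatch. The protocol does not support saying that this adjustment by itself materially biases the IT-versus-print contrast.

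The larger risk of bias is in the matched-mismatched analysis that serves the preference aim. Recall that drifts towards what worked can produce a spurious difference of about 7 to 66 min/week for shifts of 0.05 to 0.5, against a planning effect of 40. Those shifts are assumptions. The direction of the bias follows from the assumed mechanism; its size in this trial is unknown.

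**What to change.** 1. State that T2-recalled preference enters no model that estimates the randomised IT-versus-print effect. Adjust only for variables measured at baseline, for example baseline physical activity, age and gender.
2. Report the matched-mismatched analysis as exploratory, limited to T2 responders, and not as evidence of a causal effect of preference. Say that recall may depend on arm and outcome, and that the item is absent for those lost before T2.
3. Add an arm-by-baseline technology commitment interaction at T1. Table 1 shows that this scale is collected at baseline, so it is free of recall and cannot be altered by the intervention. It is a proxy for preference and imprecise: with 150 per arm split evenly into halves, the interaction has standard error 116.8 × √(4/75) = 27.0 min/week, twice the 13.5 of the main contrast.
4. Report the T1 stay-or-switch choice descriptively only. It follows 10 weeks of the assigned intervention and so cannot stand in for a pre-treatment preference.

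The cost is analysis wording; all variables are already collected. The price is that the preference result becomes exploratory. Because preference was not recorded before allocation and data collection is complete, further measurement cannot repair this.

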### Measures

The primary outcome is change in PA, which is assessed at baseline, 3 months, and 9 months using triaxial accelerometers worn at the right hip during the day over the course of 7 days and a self-administered questionnaire. Participants received the self-administered questionnaire and accelerometer at their introductory event at baseline (T0), after 3 months (T1) at their tenth group meeting, and after 9 months (T2) at their last monthly meeting. Further, due to cost issues, a random subsample of 114 participants (equally distributed across the intervention groups) underwent additional anthropometric, physical fitness, and cognitive tests to assess secondary outcomes at all 3 time points. Physical fitness was assessed using gait speed via a 4-meter walk test [29], handgrip strength using a dynamometer [30], and cardiovascular fitness using the 2-minute step test [31]. Additionally, participants’ weight was assessed using a scale. Attention and inhibition were assessed using a cognitive test (Simon task) [32].

Data from the objective measures of physical fitness and cognitive performance (Mini Mental State Examination and executive function test) will be preprocessed using customized MATLAB routines and analyzed using multivariate generalized linear models. Data for physical fitness and cognitive performance assessed at baseline and after the 10-week intervention during the first funding phase and in the subsample of participants during the second funding phase will be pooled to increase power for data analysis and to meet sample heterogeneity. Further, the larger sample size will enable us to conduct subgroup analyses with respect to motivational stage, activity behavior, and social engagement.

All participants underwent a short version of the Mini Mental State Examination during their first weekly group meeting [33]. Motivational stages to engage in recommended PA (endurance, strength, flexibility, and balance training), social-cognitive predictors for behavior change, and psychosocial factors (eg, quality of life, depression) were assessed in the self-administered questionnaire (for further detail on the instruments included in the questionnaire, see Table 1).

**Table 1 table1:** Measures assessed in the self-administered study questionnaire.

Outcome measure		Instrument/scale	Time of assessment

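### The sample size uses the SD of MVPA level while the primary outcome is change: without baseline adjustment, 80% power needs a T0-T1 correlation of about 0.44, a condition that adjusting for T0 MVPA removes

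*Protocol article*

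**What the plan says.** Analytic Strategy in the protocol article takes its variability from two earlier studies that "reported a mean 111 weekly minutes (SD 116.8 weekly minutes) of MVPA". From a larger effect reported there it scales down: "we assumed that the mean increase in MVPA in our study will reach only 40 minutes/week". It then uses those 40 minutes as the difference to be detected between groups, "with a power of 80% at an alpha of .05 (two-sided"), and concludes that "a net sample size of 150 subjects for each group is required". With about 23% loss from T0 to T1, "it is necessary to initially recruit 390 study participants (ie, 195 per group at baseline").

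Measures states "The primary outcome is change in PA", assessed at baseline, 3 months and 9 months. On the model, Analytic Strategy says "Effects of time and group (main outcomes: subjective and objective measures of PA) will be examined in multivariate analyses". It adds covariates by way of example (gender, age, preference for the material) and contextual factors. Baseline physical activity is neither named nor excluded. The article gives no SD of change and no correlation between T0 and T1.

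**The concern.** An SD quoted beside a mean of 111 weekly minutes describes how much people differ in their activity level. The variance of a change also depends on how strongly a person's T0 and T1 values are correlated. If r is below 0.5 and the two SDs are equal, change is more variable than level, so a sample sized on the level SD is too small for a comparison of changes. If r is above 0.5, it is larger than needed.

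The article names change as the outcome and time and group as the effects, but supplies only the level SD. The power claim therefore cannot be tied to the described outcome without an unstated r. Analysing T1 with T0 as covariate would largely remove that dependence, but the article does not commit to it. Study Design says the statistician is not blinded, and Results says analysis began in February 2020. Leaving the choice open therefore leaves it to someone who can see allocation.

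**Working it through.** **Inputs** (all from Analytic Strategy): SD 116.8 min/week, difference 40 min/week, two-sided alpha 0.05, power 80%, net 150 per group, loss about 23%. Not in the documents, so assumed: r is varied, and the SDs at T0 and T1 are equal unless stated.

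**1. The plan's own figure.**
- n per group = 2 × (1.960 + 0.842)² × 116.8² / 40² = 134 (135 with the t distribution). The plan states 150.
- Power at 150: standard error = 116.8 × √(2/150) = 13.49; 40/13.49 = 2.97; 2.97 − 1.96 = 1.01, which gives 84%.
- The dropout step reproduces: 150/(1 − 0.23) = 195 per group, 390 in all.

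The stated inputs thus do not lead to 150, and the surplus is about 15 per arm.

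**2. Largest SD compatible with 80% power at 150 per arm.**
- 40 / (2.802 × √(2/150)) = 123.6 min/week.

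**3. Break-even correlation for unadjusted change.**
- SD of change = 116.8 × √(2(1 − r)).
- Setting this to 123.6: r = 1 − (123.6/116.8)²/2 = 0.44 (0.443 with the t distribution).
- With 134-135 per arm the break-even would be 0.50, so 0.44 already uses the unexplained surplus.

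**4. Power at 150 per arm for 40 min/week.** Baseline-adjusted SD = 116.8 × √(1 − r²).

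| r | SD of change | Power, unadjusted change | Adjusted SD | Power, adjusted for T0 |
|---|---|---|---|---|
| 0 | 165.2 | 55.5% | 116.8 | 84.3% |
| 0.2 | 147.7 | 65.0% | 114.4 | 85.7% |
| 0.3 | 138.2 | 70.8% | 111.4 | 87.5% |
| 0.4 | 127.9 | 77.3% | 107.0 | 89.9% |
| 0.44 | 123.6 | 80.0% | 104.9 | 91.0% |
| 0.5 | 116.8 | 84.3% | 101.2 | 92.8% |
| 0.7 | 90.5 | 96.9% | 83.4 | 98.6% |

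At r = 0.3 the difference detectable with 80% power is 44.9 min/week for change and 36.2 with adjustment (t distribution). An unadjusted change analysis would need about 188 per arm.

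**5. Sensitivity to the equal-SD assumption.** Let the T1 SD be k times the T0 SD. The break-even solves 116.8² × (1 + k² − 2rk) = 123.6². It is r = 0.32 at k = 0.8 and r = 0.55 at k = 1.2. The adjusted analysis also depends on the T1 SD: at k = 1.2 that SD is 140.2, and 140.2 × √(1 − r²) ≤ 123.6 needs r of at least 0.47. The condition is still weaker than for change.

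**The case against.** The strongest reply is that the article does not fix an unadjusted change-score analysis. Change is often analysed by adjusting follow-up for baseline, and the covariate list is introduced as examples, so T0 MVPA is not ruled out. The exact model and the assumed correlation commonly belong in the full protocol or the analysis plan, which are not shown. For a baseline-adjusted analysis the level SD is conservative at any non-zero r, and for change scores it is conservative once r exceeds 0.5. Nothing in the article suggests that r is below 0.44. Data collection has ended, so the sample size cannot change.

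Most of this stands. A reader might infer that the trial is underpowered, or that its 80% holds only if r reaches 0.44 whatever the analysis. The documents support neither: the threshold needs an unadjusted (or unconstrained time-by-group) contrast and equal SDs, and no r is reported. A reader might also take the covariate list as proof that baseline is left out, but its wording does not carry that.

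What does not fall is the mismatch inside the published text. The article states a power, an outcome and an SD, and that SD does not by itself belong to that outcome. A time-by-group contrast without a constraint on the baseline means is a natural reading, and it is equivalent to comparing changes.

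A separate reservation applies to every power figure here. The article introduces 40 min/week as a mean increase and then uses it as a difference from a control group, while the Discussion says that the trial has no control group. The figures take it as the IT-versus-print difference.

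**Conclusion.** The point holds in conditional form. A level SD was used to size a trial whose primary outcome is change, and neither the correlation nor a baseline-adjusted analysis that would make this harmless is stated. Whether power falls short depends on an r that the documents do not give. At r = 0.3 the choice between the two analyses is worth about 17 percentage points (70.8% against 87.5%).

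The assurance of at least 84% with adjustment rests on 40 min/week being the between-arm difference, 150 analysable participants per arm, and a T1 SD no larger than 116.8. This is an improvement that should be made, not evidence that the trial fails. Whether the accelerometer or the questionnaire is the primary measure is a separate issue.

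**What to change.** State that the between-arm comparison of MVPA at T1 is adjusted for T0 MVPA. Add a sensitivity analysis without T0, because Study Design places the start of T0 data collection at the introductory event where participants learned their allocation, so T0 values may already reflect it.

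Restate the power for the adjusted model over a range of r, for example 0.3 to 0.7 (87.5% to 98.6% under the assumptions above). Say that SD 116.8 and a difference of 40 require about 135 per arm, and explain how 150 was reached. If an unadjusted change analysis is kept instead, state the SD of change or the r assumed.

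The cost is analysis wording only: T0 and T1 are already scheduled assessments, and no new data are needed. Because analysis has begun and the statistician is unblinded, record when the choice of model was made.

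### The only 9-month comparison that is specified and sized is between four pathways participants choose themselves, so its differences mix intervention effects with self-selection

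*Protocol article*

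**What the plan says.** Participants are randomised equally to the IT-based or the print-based intervention. Under Study Design: "Participants were given the choice to remain in their intervention group or to cross over to the other group after 3 months". The same section says that participants are not blinded and that preference for the material is asked retrospectively at 9 months.

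For T2 the Analytic Strategy states "we expect that approximately 240 individuals at T2 will self-select to one of the 4 groups: IT-IT, print-print, IT-print, or print-IT". The sizing rests on a condition about the split, "Should participants self-select equally into each group (n=60"). Given that condition, the claim made for T2 is that "we will still be able to detect the mean difference of 77 minutes/week [28] between each group". On the method, the section says only that this is done "by means of an appropriate post hoc test that is adjusted for multiple comparisons".

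The same section opens with a general statement that effects of time and group on the PA outcomes will be modelled, with covariates such as gender, age, preference and context. It does not say whether group means randomised arm or chosen pathway. Measures defines the primary outcome as change in PA, assessed at baseline, 3 and 9 months. The Abstract gives effectiveness of IT-based versus print-based delivery over 9 months as the aim. The Discussion lists three limitations: no control group, difficult recruitment, and recall bias in the preference item.

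**The concern.** Randomisation protects a comparison of IT with print. It does not protect a comparison of IT-IT with IT-print, because membership is decided by the participant after three months of seeing how things went. A difference between pathways at T2 can come from the material, from the kind of person who stays or switches, or from both, and the test cannot tell these apart.

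Adjusting for multiple comparisons controls chance findings across pairs and does nothing about selection. The named covariates help only in part: activity at T1 is not among them, and preference is recalled at T2, after both the choice and the outcome period.

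If the pathway contrasts were reported as the 9-month answer to IT versus print, a difference due to choice could be read as effectiveness. The Discussion expects the results to support permanent health insurance funding, so that reading has consequences.

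**Working it through.** **Inputs from the Analytic Strategy.** The section cites studies that "reported a mean 111 weekly minutes (SD 116.8 weekly minutes) of MVPA". For the T1 comparison, "we assumed that the mean increase in MVPA in our study will reach only 40 minutes/week", "with a power of 80% at an alpha of .05 (two-sided), a net sample size of 150 subjects for each group is required". Losses are about 23% to T1 and a further 20% to T2. Power and alpha are not restated for T2, so I carry over 80% and 0.05 two-sided. The post hoc test is not named; I assume Bonferroni.

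**1. The plan's own T2 figure.**
- Numbers: 390 × 0.77 ≈ 300; 300 × 0.80 = 240; 240/4 = 60.
- Pairs: 4 × 3/2 = 6, so alpha per pair = 0.05/6 = 0.0083.
- Standard error: 116.8 × √(2/60) = 21.3; 77/21.3 = 3.61.
- Power is 82% with the noncentral t (83% with the normal approximation). The statement reproduces.

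**2. Dependence on the equal split.** Suppose instead that 80% of each arm stays (my assumption), giving 96 stayers and 24 switchers per arm. For 77 min/week at alpha 0.0083:
- 96 v 24: standard error 116.8 × √(1/96 + 1/24) = 26.7; power 58%.
- 24 v 24: standard error 116.8 × √(2/24) = 33.7; power 33%.

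**3. The randomised comparison with the same 240 people.** 120 v 120, alpha 0.05:
- Standard error: 116.8 × √(2/120) = 15.1.
- Detectable at 80% power: (1.96 + 0.84) × 15.1 ≈ 42 min/week (42.4 with the t distribution).
- For 40 min/week: 40/15.1 = 2.65; power about 75%.

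**4. How large could selection be?** Take no intervention effect and a common SD of 116.8 at T0, T1 and T2. Let the log-odds of staying be b × Z, where Z is the standardised quantity that drives the choice; half then stay. The stayer-minus-switcher gap in Z is 4 × E[Z × expit(bZ)], which is 0.472 for b = 0.5 and 0.826 for b = 1.0 by numerical integration. The difference in T0-to-T2 change is that gap times Cov(Z, Y2 − Y0). I assume T0–T1 and T1–T2 correlations of 0.6.
- Choice follows T1 level: Cov = 116.8 × (0.6 − 0.6) = 0, so the bias is about 0. This relies on the two correlations being equal.
- Choice follows T0-to-T1 change: Cov = 116.8 × (1 − r02)/√0.8, where r02 is the T0–T2 correlation.
  - r02 = 0.6: 116.8 × 0.447 × 0.472 = 24.7 min/week.
  - r02 = 0.4: 116.8 × 0.671 × 0.472 = 37.0 min/week.
  - With b = 1.0 these become about 43 and 65 min/week.

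None of these slopes or correlations is in the article. They show a range and are not an estimate for this trial. Comparing arms as randomised pools stayers and switchers within each arm, so this selection does not enter it.

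**The case against.** The strongest reply is that the main analysis is the time-and-group model. Study Design uses the word group for the randomised arms, the Introduction states the main aim as IT versus print, and a condensed article need not spell out every contrast. This stands in part. A reader might infer that the trial replaces the randomised arms with the pathways at 9 months. The document does not say that; a time-by-arm model is a fair reading. What remains is that group is undefined, no sentence commits to arms at T2, and the one T2 contrast that is fixed, with groups, effect size and type of test, is the non-randomised one.

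Three other strong readings also fail:
- That pathway differences say nothing about the intervention. They are confounded with choice, so both effects are mixed.
- That stayers are bound to look better. Nothing in the article shows this. Choice may follow format, usability or ease with technology. A bias computed on T2 level alone (0.6 × 116.8 × 0.472 ≈ 33 min/week) does not apply as it stands, because the stated outcome is change.
- That the 77 min/week claim is a power error. It reproduces, its source is cited, and the equal split is an open condition.

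The article also says plainly that participants self-select, never calls the pathway contrasts confirmatory, and studies preferences as a legitimate aim. All of that stands, and is a reason to keep the pathways with a clear label.

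**Conclusion.** The concern holds in limited form. The only T2 comparison specified and sized is between groups formed by choice after randomisation. Its planned adjustments do not remove selection, and selection is not among the stated limitations. Used for the 9-month IT-versus-print aim, it would give confounded answers.

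The possible bias runs from about 0 to about 25–37 min/week under the models above (43–65 with the steeper slope). Either sign is possible if choice works differently. For scale, the effect assumed for T1 is 40 min/week.

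The T1 comparison, for which the 390 was set, precedes any switching and is untouched. The point therefore concerns the 9-month claim and not the trial as a whole.

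**What to change.** 1. State that the main T2 effectiveness analysis compares the arms as originally randomised, regardless of switching, adjusted for T0 PA. Say that it estimates the effect of initial assignment followed by free choice.
2. State its precision: expected 120 v 120, about 42 min/week detectable at 80% power, about 75% power for 40 min/week (unadjusted t-test, SD 116.8).
3. Keep the four-pathway contrasts for the preference aim, labelled exploratory and non-randomised, adjusted for T0 and T1 PA and T0 covariates, with no effectiveness claim.
4. Keep the 77 min/week statement only as conditional on an equal split (about 82% power with Bonferroni over six pairs), with an unequal example such as 58% for 96 v 24 and 33% for 24 v 24.
5. Add self-selection into the T2 pathways to the limitations.

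This is a change of wording and needs no new data. The cost is that the pathway contrasts carry less inferential weight, and that the stated T2 power for 40 min/week falls slightly below 80%. The article reports that analysis began in February 2020, so the change should be dated relative to any look at T2 results.
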